different individuals (interindividual variability), the variability within the same individual when taking the drug on more than one occasion (intraindividual variability) and the so-called residual variability or not explained by the model, both in kinetic (drug concentrations) and dynamic processes (pharmacological effect). Finally, the population PK/PD analysis provides the ability to identify and quantify the effect that different individual characteristics (genetic, demographic, clinics ...) may have on each of the parameters describing these processes, permitting us to individualize the dose of the drug according to individual characteristics.

In this study, the information obtained will be of great clinical utility. Knowing those variables that may influence RMD pharmacokinetics and pharmacodynamics, will help to better define a therapeutic range of RMD to trigger HIV latency reactivation to be combined with therapeutic vaccines, and thus, identify more precisely the RMD dose that each patient should receive in order to maintain drug exposure within the desired range.

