### Correlates of Control:

As mentioned above, a better definition of immune correlates of viral control is urgently needed to selectively conduct future treatment interruptions in subpopulation of participants with highest chance of success after cessation of treatment and to minimize risks for participants.

If efficacy clinical outcomes during the MAP phase are achieved during the BCN02-Romi trial, study of correlates of control will be carefully performed to identify best predictors using multivariate regression and omic data integration techniques.

**In summary, BCN02-Romi study is the first vaccine/eradication proof-of-concept clinical trial aiming to evaluate a combined "kick and kill" strategy using the most immunogenic candidate vaccines available so far (HIVconsv) with the strongest LRA available at present time (RMD). In addition, early treated HIV positive individuals poses an optimal target population to prove the effect of such a strategy in reducing the viral reservoir and containing viral rebound after a very well planned treatment interruption phase using a MAP strategy. Here, and through the development of a population PK/PD analysis, we will analyse the *in vivo* effects of RMD in the induction of HIV expression in resting cells, deeply investigate any unintended effect on the CTL function as well as predict the relationship between RMD exposure and such effects. Finally, our results will allow us to optimize RMD dosing, to evaluate the clinical efficacy of this strategy after the cART interruption and to identify better correlates of control of rebound viremia after cessation of treatment.**

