## 3.1 HYPOTHESIS

1. Administration of RMD (5 mg/m^2) to early-suppressed HIV infected individuals and whose CTL response has been refocused to more conserved regions of HIV by HIVconsv therapeutic vaccines will be safe and will reduce the viral reservoir.
2. Both HIV reactivation as well as, in case it is confirmed, eventual toxicity on CTL functionality by RMD, will be related to the exposure to RMD, allowing the definition of a RMD therapeutic range in this specific scenario.
3. After RMD administration, efficient re-stimulation of the cytotoxic response will be reached by MVA.HIVconsv, and the immunogenic response will be associated to the level of immune control after a monitored antiretroviral pause.

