### 5.3.2 Secondary endpoints

1. To evaluate *ex vivo* capacity of RMD to induce HIV expression in resting CD4+ T cells and to influence CTL functionality. Stored biological samples from the BCN01-RO phase will be used. Culture incubations with RMD will simulate Cmax concentrations of the clinical dose ( $5\text{mg}/\text{m}^2$ ). Results of the *ex vivo* system will be associated with the frequency of detected HIVconsv-specific induced T cells and compared to the observations during the intervention phase to assess its *in vivo* translation. *Ex vivo* measurements will include:
  - 1.1. Cell-associated RNA (CA-RNA)
  - 1.2. Viability, necrosis and apoptosis levels by flow cytometry and using Annexin, 7AAD, CD3, CD4 and CD8 markers
  - 1.3. Activation, exhaustion and proliferation capacity
  - 1.4. IFN $\gamma$  production assessed by ELISPOT and after PBMC stimulation with HIVconsv-specific peptides, as well as other non-related pathogens, such as EBV and CMV.
  - 1.5. Evaluation of the in-vitro viral inhibition capacity in the presence of RMD to a panel of 3 viruses (CCR5 and CxCR4)
2. To perform a population PK/PD analysis to assess the relationship between HIV expression and CTL functionality effect *in vivo* with RMD exposure. Specific endpoints will include:
  - 2.1. RMD plasma concentrations at the end and 0.5, 1, 2, 4, 8, 10 and 20 hours after the 1st RMD infusion. RMD plasma concentrations at the end and 8

- hours after the 2nd and 3rd infusions. Plasma concentrations will be measured by LC-MS/MS, and will be used to develop a population PK model. Parameters will include: volumes of distribution, total and intercompartmental plasmatic clearance, maximum and minimum concentrations and area under the curve.
- 2.2. *In vivo* capacity of RMD to induce HIV expression in resting CD4+ T cells measured by CA-RNA and ultrasensitive plasma viral load (SCA) before RMD infusion and after 24 and 72h (RMD1), 12 and 72h (RMD2) and 12, 72 and 7 days (RMD3)
  - 2.3. *In vivo* levels of Histone H3 acetylation in lymphocytes before RMD infusion and after 24 and 72h (RMD1), 12 and 72h (RMD2) and 12, 72 and 7 days (RMD3)
  - 2.4. *In vivo* IFN $\gamma$  production assessed by ELISPOT and after PBMC stimulation with HIVconsv-specific peptides before RMD infusion and after 24 and 72h (RMD1), 12 and 72h (RMD2) and 12, 72 and 7 days (RMD3)

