## 5.4 MEASURES TO AVOID BIAS

All patients will receive the same treatment in this study.

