#### 6.3.1 Romidepsin (RMD, Istodax®)

Dose: 5mg/m^2 over 4hours  
Interval: weeks 3, 4 and 5

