Population PK/PD analysis: Briefly, a pharmacokinetic model will be developed using a population approach by means of the software NONMEM 7.3. The population approach allows us, through an intensive modelling exercise, to analyze the data from all participants at the same time but keeping their individual origin. Therefore, estimates for the pharmacokinetic parameters describing not only the mean tendency of the concentration-time course in the population but also at the individual levels will be obtained. The main steps to develop the proposed population pharmacokinetic model are: 1) The pharmacokinetic profile of RMD using the data from the experimental phase of the project will be established: one, two or three compartment models to describe RMD pharmacokinetics will be assessed; 2) Interindividual variability in RMD pharmacokinetic parameters as well as interoccasion variability will be determined, and; 3) The influence of individual characteristics (covariates) in RMD pharmacokinetic parameters will be incorporated into the model. This process will consist of two steps: *forward inclusion* and *backward elimination*. Statistical significance cut-offs for retaining a covariate into the model during the *forward inclusion* and the *backward elimination* steps will be 0.05 and 0.01, respectively. In addition, those covariates without clinical

plausibility will be removed from the model. Once the model had been developed, its predictive capacity will be evaluated by means of simulation and resampling methods (Monte Carlo and bootstrapping, respectively). The final model will be used to evaluate the relationship between RMD exposure and the magnitude of either inhibition of histone deacetylation, HIV reactivation and CTL. Full RMD pharmacokinetic profiles after each RMD dose will be simulated, and area under the curve, maximum and minimum RMD concentrations in plasma will be determined at each occasion and for each participant. A PK/PD analysis will be carried out to evaluate the relationship between each PK parameter and each pharmacodynamic endpoint (lineal, exponential or maximum effects models will be tested). The results from this analysis will be used to determine, through simulation exercises, the dose of RMD to be given to each particular patient to maximize the chances to get the desired effect with minimum risk of deleterious effects.

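### From one romidepsin dose level the PK/PD plan promises a therapeutic range and individual doses; the claim should be limited to observed exposures, and unequal early reading times should be handled

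*Protocol*

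**What the plan says.** **Design.** Protocol 6.3.1 fixes one romidepsin dose level ("Dose: 5mg/m 2 over 4hours"; "Interval: weeks 3, 4 and 5"), and 5.4 states "All patients will receive the same treatment in this study". The ex vivo work in 5.3.2 also targets a single concentration, the peak for that same dose. Section 10.3 caps enrolment at 24 and describes a pilot able to detect only a large effect.

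**Claims.**
- Hypothesis 2 (3.1) links reactivation and any CTL toxicity to exposure, "allowing the definition of a RMD therapeutic range in this specific scenario".
- The population PK/PD part of section 3 expects to "identify more precisely the RMD dose that each patient should receive".
- The closing summary of section 3 says "our results will allow us to optimize RMD dosing".
- Section 10.1 says, without a condition, that the results will be used to determine "the dose of RMD to be given to each particular patient to maximize the chances to get the desired effect".

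**Method and sampling.** Section 10.1 derives AUC, maximum and minimum concentration at each occasion for each participant. It relates each of these to each effect endpoint, trying linear, exponential and maximum-effect curves. Effects are read before each infusion. For dose 1 the plan has "ultrasensitive plasma viral load (SCA) before RMD infusion and after 24 and 72h"; for dose 2 the later readings are at 12 and 72 h, and for dose 3 at 12 h, 72 h and 7 days. Histone acetylation, ELISPOT and the CTL toxicity marker follow the same times.

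**The concern.** A therapeutic range or an individual dose is a statement about what would happen if the dose were changed. Here the dose is never changed. Patients with higher exposure at the common dose are those with lower clearance for some reason, and that reason may itself affect reactivation or CTL function. Dose proportionality is untested, and any simulated dose whose exposure falls outside the observed spread relies on the chosen curve alone. A later trial could adopt a range or dose that these data do not establish.

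A smaller problem sits beside it. If the first post-dose effect reading is pooled or compared across doses against AUC, Cmax or Cmin, a difference between dose 1 and the later doses could reflect only the later clock time of the dose 1 reading.

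**Working it through.** The Protocol has no PK/PD precision or power figure to reproduce; 24 is the size of the source cohort. It gives no exposure CV, residual SD or effect half-life, so every value of these below is an assumption, shown as a range.

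**1. Schedule counts (5.3.2).** Dose levels: 1. PK samples after infusion: 8 + 2 + 2 = 12 per patient, or 12 × 24 = 288 at most. Post-dose effect readings: 2 + 2 + 3 = 7 per patient.

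| Reading | Dose 1 | Dose 2 | Dose 3 |
|---|---|---|---|
| Pre-dose | yes | yes | yes |
| 12 h | no | yes | yes |
| 24 h | yes | no | no |
| 72 h | yes | yes | yes |
| 7 days | no | no | yes |

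**2. Exposure seen at one dose.** For log-normal exposure, σ = √ln(1 + CV²), and the 5th to 95th percentiles are exp(±1.645σ) times the median.
- CV 30%: σ = 0.294, range 0.62–1.62
- CV 50%: σ = 0.472, range 0.46–2.18
- CV 70%: σ = 0.631, range 0.35–2.83

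**3. What 24 patients could estimate inside that range.** Simulation, 400 trials per setting: a true maximum-effect curve with EC50 at the median exposure and one effect reading per patient. Maximum-effect and linear curves (two of the three planned forms) were compared by AICc.

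| Residual SD (share of Emax) | CV | EC50 within 2-fold | True curve preferred to linear | Power for any slope |
|---|---|---|---|---|
| 0.1 | 30% | 0.76 | 0.66 | 0.88 |
| 0.1 | 50% | 0.89 | 0.77 | 0.99 |
| 0.1 | 70% | 0.97 | 0.88 | about 1.00 |
| 0.3 | 30% | 0.30 | 0.40 | 0.18 |
| 0.3 | 50% | 0.45 | 0.58 | 0.34 |
| 0.3 | 70% | 0.52 | 0.66 | 0.47 |

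If only 15 patients contributed (an assumption), the EC50 would be within two-fold in 61–88% of trials with precise readings and 20–38% with noisy ones.

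**4. Beyond that range.** At three times the median exposure the true effect in this model is 3/(1 + 3) = 0.75 of Emax. With n = 24 and residual SD 0.1, the fitted linear curve exceeds the fitted maximum-effect curve there by a median of 0.18 of Emax at CV 30%, where that exposure is well outside 0.62–1.62. At CV 70%, where it is only just outside 0.35–2.83, the gap is 0.06. The further outside the data, the more the curve choice decides the answer.

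**5. Using all three occasions, as 10.1 intends.** With n = 24, AUC CV 40%, SD of log effect 0.4, assumed interoccasion CV 20% and independent residuals, the 5–95% range of the estimated EC50 (true value 1) is 0.47–2.26, a span of 2.26/0.47 = 4.8-fold. Allowing residuals to correlate within a patient widens it to about 0.3–2.9. In a noisy setting it is about 0.03–26.

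**6. Reading time.** If an effect decays with half-life T, the 24 h value is 2^(−12/T) of the 12 h value:
- T = 6 h: 0.25
- T = 12 h: 0.50
- T = 24 h: 0.71
- T = 48 h: 0.84

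So a ratio of 0.25 to 0.84 would appear between dose 1 and the later doses with no true difference.

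**The case against.** The best defence has four parts.

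- **Exposure does vary.** Between-patient and between-occasion variability give a usable range, and 10.1 models both. Simulating one occasion per patient understates the information, as step 5 shows. This stands. It is why a relation inside the observed range should be described and not forbidden.
- **The stakes are modest.** PK/PD is a secondary endpoint in a declared pilot, section 3 partly says only that results will help to better define a range, and no participant's dose depends on the model. This lowers the urgency. It does not qualify the sentence in 10.1, which carries no condition.
- **Unequal times can inform a time course.** Section 3 speaks of modelling the effect over time. The PK labels in 8.1.4 (−4 h before infusion, 20 h next morning) suggest a zero at the end of the 4 h infusion. If the effect times run from the start of infusion, 24 h pairs with the 20 h PK sample and 12 h with the 8 h sample. The Protocol does not state the zero for the effect times, so this is an inference. A time-based model could use the readings, and the times fit the observation periods in 6.3.1 (24 h after dose 1, 12 h after doses 2 and 3). This also stands.
- **Most comparisons are unaffected.** All doses share pre-dose and 72 h readings, and doses 2 and 3 share 12 h. Only the early contrast of dose 1 with the later doses is confounded.

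A reader might infer that time and dose number can nowhere be separated, or that an extra effect reading at dose 1 is required. The shared readings rule out the first, and a time-course model makes the second an optional sampling preference.

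**Conclusion.** The point holds as a claim that exceeds its design. One dose level, unassigned exposure and at most 24 patients can support an exploratory exposure-effect description within the exposures seen. They do not establish a therapeutic range or a dose for each patient, and they offer nothing but extrapolation beyond those exposures. Confounding with the determinants of clearance remains however precise the readings are.

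A reader might go further and infer that no dose-related conclusion is possible, or that the curve would be picked more or less at random. The documents do not support that. With assumed exposure CVs of 30–70%, success in placing the EC50 runs from 30% to 97% of trials, depending mainly on a residual SD the Protocol does not give, and three occasions can improve on one.

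The time mismatch is secondary. It is confined to the 24 h versus 12 h contrast and matters only if those readings are pooled or compared as equivalent. This is a wording and analysis correction to a secondary endpoint. The safety and reservoir endpoints are untouched.

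**What to change.** 1. In section 3 (the population PK/PD part and the closing summary), hypothesis 2 in 3.1, and the last sentence of the PK/PD paragraph in 10.1, state that exposure-effect relations will be described, with their uncertainty, only within the exposures observed at the studied dose, and labelled hypothesis-generating. Add that no simulation outside that range will be presented as a dose recommendation.
2. In 10.1, state that effects will be compared across doses only at shared times (pre-dose and 72 h for all three; 12 h for doses 2 and 3), or that reading time will be modelled explicitly. State that the 24 h and 12 h readings will not be pooled against AUC, Cmax or Cmin as if equivalent.

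The cost is a few sentences and a more modest claim. No visit, sample or assay needs to be added, and no dose or clinical rule is proposed.

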## 10.2 SECURITY ANALYSIS

In addition to safety description analysis, stopping rules will be established for the two parts of the study as follows:

a) Stopping rules during the Part A of the study will be based on the observation of an unexpected high proportion of individuals experiencing any AE/SAE to any of the vaccinations and/or RMD administration as described in section 5.6.

b) On the other side and in order to minimize risks of the intervention, an early interim and futility analyses is planned for each individual before the MAP phase. Acceptability for cART interruption after interim analyses will be reviewed. Treatment interruption would be discouraged individually if a) boosting MVA.HIVconsv was shown to be no longer immunogenic after RMD administration (no net increase in induced response compared to pre-vaccination levels with MVA.HIVconsv at BCN02-Romi baseline visit) and/or b) persistent detectable viremia. Limited MVA.HIVconsv immunogenicity after MVA2 may indicate RMD toxicity on CTL functional activity for instance; therefore, an improved viral control would not be foreseen. On the other hand, increases in immune activation shortly after immunization are expected to decrease 8 weeks after vaccination. However, in some cases, intermittent detectable plasma low-level viremia have also been reported to occur after vaccination, which may induce an extended immune activated status that could favor a faster and higher viral rebound after treatment cessation. Therefore, clinical team will discuss cases where treatment interruption could be also discouraged in cases with persistent detectable viremia (i.e. longer than 12 weeks after last immunization)

In all cases where immune and/or virological futility criteria are not met and treatment interruption is discouraged, trial results would be focused on the viral reservoir and immunogenicity endpoints only until better correlates of control would be available to predict clinically relevant outcomes on which one could recommend treatment interruptions in a safer manner.

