## 5.6 END OF TRIAL

Stopping rules will be based on the observation of an unexpected high proportion of individuals experiencing SAE or any grade  $\geq 3$  local or systemic events judged definitely or probably related to any of the vaccinations and/or romidepsin administration.

If two or more study participants develop a clinically similar SAE or grade 3 local or systemic event, judged definitely, or probably related to the investigational medicinal products (IMP)s, a review by the Scientific Committee will be requested. The study will be suspended pending review of all safety data. Following this review, the Scientific Committee will make a recommendation to the Principal Investigator and Sponsor regarding continuation of the study (see section 9.3 for details)

In addition, if more than 50% of participants withdraw from the Scientific Committee will discuss a premature stop of the trial.

The date of the end of the trial will be to the last visit of the last patient.

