## 6 TRIAL INVESTIGATIONAL PRODUCT(S)

### 6.1 EXPERIMENTAL TREATMENT

Two investigational medicinal products (IMP)s will be tested in this trial:

- Vaccine MVA.HIVconsv 2x10^8 pfu, an investigational immunological product (vaccine) from a biological / biotechnological origin that contain genetically modified organisms.
- Romidepsin (Istodax®) 5mg/m^2, administered after antiemetic ondansetron 8mg intravenous (iv) infusion.

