##### Definitive:

- A plausible time sequence exists in relation to administration of the drug or its plasma or tissue concentrations.
- The observed manifestation coincides with the known adverse reactions profile of the implicated drug.
- The event cannot be explained by the concurrent disease or by other drugs or chemical substances.
- Response to withdrawal must be clinically plausible, i.e., the condition improves on discontinuing administration of the drug.
- A positive response to repeat exposure is observed.

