##### Probable:

- A reasonable time sequence exists in relation to administration of the drug.
- The observed manifestation coincides with the known adverse reactions profile of the implicated drug.
- The event is unlikely to be explained by the concurrent disease or by other drugs or chemical substances.

- Response to withdrawal is clinically plausible, i.e., the condition improves on discontinuing administration of the drug.
- No repeat exposure is required to complete this definition.

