## 9.7 SCIENTIFIC COMMITTEE

A Scientific committee will be formed to review clinical data and stopping rules. The committee will be composed of the coordinating investigator plus two physicians of the investigator team and one external physician. See attachment P for details

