#### 9.8.4 Reporting by Sponsor to Coordinating investigator

The Sponsor will inform the Coordinating investigator of all SAEs within 24 hours in order that the Coordinating investigator can call the scientific committee to assess trial stopping rules.

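### No count in the protocol text obliges study-level review of severe events attributed to stopping cART, although Section 10.2 announces stopping rules for both parts

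*Protocol*

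**What the plan says.** - **Section 10.2** introduces its two items with "stopping rules will be established for the two parts of the study as follows". Item (a), labelled Part A, refers to Section 5.6. Item (b) is the Part B item: "an early interim and futility analyses is planned for each individual before the MAP phase". Under it, interruption is discouraged person by person, for lack of a net immune response or for persistent viremia.
- **Section 5.6** holds the only event count. When two or more participants have a clinically similar SAE or grade 3 event "judged definitely, or probably related to the investigational medicinal products (IMP)s, a review by the Scientific Committee will be requested", and the study is suspended until the review is done. A separate clause has the committee discuss stopping if more than half of participants withdraw.
- **Section 6.1** defines the products: "Two investigational medicinal products (IMP)s will be tested in this trial". They are MVA.HIVconsv and romidepsin.
- **Section 9.4.3** sets the causality grades. The definitive grade requires: "The event cannot be explained by the concurrent disease or by other drugs or chemical substances". The probable grade requires: "The event is unlikely to be explained by the concurrent disease or by other drugs or chemical substances".
- **Section 9.7**: "A Scientific committee will be formed to review clinical data and stopping rules". **Section 9.8.4** sends every SAE to the coordinating investigator within 24 hours "in order that the Coordinating investigator can call the scientific committee to assess trial stopping rules".
- **Sections 8.1.15 and 8.1.16** provide visits with graded symptoms of acute retroviral syndrome, weekly for 12 weeks and then fortnightly. They recommend immediate restart of cART for confirmed viral load above 2,000 copies/mL, symptoms, laboratory abnormalities or a significant CD4 drop.

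**The concern.** Item (b) decides whether one person may begin the pause. It is finished once the pause begins, so it cannot respond to harm seen during the pause. The remaining study-level event rule depends on causality to a product, whereas the characteristic harm of the pause comes from the underlying infection once cART is withdrawn. Section 5.3.2 (endpoint 3.5) foresees symptomatic acute retroviral syndrome and CD4 decline as reasons to restart, and symptom severity is graded at every pause visit. The data needed for a collective safeguard are therefore collected, but no count uses them.

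At stake is whether participants still on cART would be asked to stop it after two others had a similar severe event, without anyone having been required to look at those two cases first.

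**Working it through.** **1. Would a severe pause event count under Section 5.6?** Take two participants with grade 3 acute retroviral syndrome after stopping cART.

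| Route | What it needs | Does it oblige review here? |
|---|---|---|
| 10.2(b) | Individual immunogenicity and viremia check before the pause | No: it is over before the event |
| 5.6, event count | Definite or probable relation to MVA.HIVconsv or romidepsin | Ordinarily no: under 9.4.3 the concurrent disease must be excluded, or be an unlikely explanation, and here HIV is the explanation |
| 5.6, withdrawals | More than 50% withdraw | No: counts withdrawals, not harms |
| 9.7 | Committee reviews clinical data and stopping rules | It may review; no count requires it |
| 9.8.4 | An SAE is reported | The committee can be called, to assess the same rules; non-serious grade 3 events do not enter this route |
| 8.1.16 | Individual restart criteria | No: acts on the affected person only |

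**2. How many people would a trigger protect?** The plan states no figure to reproduce. From the protocol: at most 24 participants (10.3) and a 6-month inclusion period (5.5), taken as 26 weeks. Assumed: n participants start the pause at even spacing s = W/(n − 1) over W weeks; event rates p of 2%, 5% or 10%; events independent between participants.

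The chance that the second affected participant, in order of pause start, is number k is (k − 1)p²(1 − p)^(k−2). Conditioning on at least two events among 24 gives the median k:

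| p | P(at least 2 of 24) | Cumulative probability just below the median | At the median | Median k |
|---|---|---|---|---|
| 2% | 0.083 | 0.482 (k = 16) | 0.540 | 17 |
| 5% | 0.339 | 0.451 (k = 14) | 0.504 | 15 |
| 10% | 0.708 | 0.482 (k = 12) | 0.535 | 13 |

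If the second event comes t weeks into the pause of participant k, the number already started is min(n, k + floor(t/s)). With n = 24 and W = 26, s = 26/23 = 1.13 weeks, so floor(4/1.13) = 3 and floor(12/1.13) = 10.

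- At 4 weeks: 24 − (17 + 3) = 4; 24 − (15 + 3) = 6; 24 − (13 + 3) = 8 not yet paused.
- At 12 weeks: 17 + 10 and 15 + 10 both exceed 24, so 0 and 0; 24 − (13 + 10) = 1.

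**3. Sensitivity.**

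| Pausing | Entry | Not yet paused at 4 weeks (2% / 5% / 10%) | At 12 weeks |
|---|---|---|---|
| 24 | 26 weeks | 4 / 6 / 8 | 0 / 0 / 1 |
| 24 | 13 weeks | 0 / 2 / 4 | 0 / 0 / 0 |
| 24 | 4 weeks | 0 / 0 / 0 | 0 / 0 / 0 |
| 12 | 26 weeks | 2 / 2 / 3 | 0 / 0 / 0 |

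For 12 pausing, the median k is 9, 9 and 8, and s = 26/11 = 2.36 weeks.

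**4. How often would it fire?** P(at least 2) = 1 − (1 − p)^n − np(1 − p)^(n−1). At 2%, 5% and 10% this is 0.08, 0.34 and 0.71 for n = 24; 0.05, 0.23 and 0.55 for n = 18; 0.02, 0.12 and 0.34 for n = 12. These are upper limits, because the events must also be clinically similar.

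**5. Room for a hold.** The second vaccination is at week 9. The pause is due at 9 + 8 = week 17 and the immune result is valid to 9 + 12 = week 21 (7.3.4). Slack: 21 − 17 = 4 weeks, or 28 days.

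**The case against.** The other side has real weight. Section 10.2 never says that a stopping rule must be collective, and an individual bar on stopping cART is a coherent rule for a single-arm pilot of at most 24. Monitoring in the pause is close, and restart is aimed at within 10 days of the first positive qualitative test. The coordinating investigator sits on the Scientific Committee and hears of every SAE within 24 hours whatever its cause, and under Section 8.1.14 a study physician confirms each interruption with the participant. All of this stands. It narrows the gap to the lack of an obligatory count, felt most for grade 3 events that are not serious.

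Three stronger readings are tempting and not supported:

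- A reader might infer that Part B has no study-level safety rule at all. Section 5.6 has no part limit, so product-related events after the second vaccination still trigger review.
- A reader might infer that the plan certainly contains no such trigger. Attachments M, P and AB are not shown, and Section 9.7 refers to P for committee details. The claim reaches only as far as the visible text.
- A reader might picture an early second event with most of the cohort still to pause. If it fell in participant 6, 15 of 24 would remain at 4 weeks and 8 at 12 weeks. But the chance of two affected among the first six is only 0.006 at a rate of 2%, 0.033 at a rate of 5% and 0.114 at a rate of 10%, so this is not the expected benefit.

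**Conclusion.** The point holds in a limited form. Section 10.2 announces stopping rules for both parts, its Part B item is individual and precedes the pause, and the Section 5.6 count, followed as written, would ordinarily leave out severe events attributed to stopping cART. The remaining safeguards are individual or discretionary.

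The gain from closing the gap is modest. At the median position of the second event it is 4 to 8 participants not yet paused at 4 weeks, and 0 or 1 at 12 weeks, with 24 pausing evenly over 26 weeks. It shrinks to few or none with faster entry or fewer pausing. The event rates, even spacing and independence are assumptions; the protocol gives no rate for such events. The change is still worth making, because it concerns participant safety and costs little. Confidence is medium because of the unseen attachments.

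**What to change.** Add to Sections 5.6 and 10.2(b):

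> If two or more participants develop a clinically similar SAE or grade ≥3 clinical event (including acute retroviral syndrome of grade ≥3) judged related to cART interruption, whatever its relation to the IMPs, the Scientific Committee will review it before further participants start the pause. Viral rebound or a CD4 decline that meets a restart criterion without such an event does not count. Participants already in the pause continue under 8.1.16.

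The exclusion is confined to rebound and CD4 decline on purpose. Symptoms are themselves a restart reason, so excluding restart criteria in general could remove acute retroviral syndrome, the event that the trigger is for. If Attachment P already holds such a rule, a cross-reference from 5.6 and 10.2(b) is enough.

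The cost is a few lines of text, with the existing committee and data already collected. The downside is a short hold for those about to pause. Anyone held beyond week 21 needs a repeat ELISPOT.
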